### Compliance

Compliance was assessed clinically on a per patient per visit.$$\mathrm{Compliance}\left(\%\right)=\frac{\mathrm{Actual}\ \mathrm{number}\ \mathrm{of}\ \mathrm{treatments}}{\mathrm{Planned}\ \mathrm{number}\ \mathrm{of}\ \mathrm{treatments}}\times 100$$

Records of the study medical device used, the number of treated, and intervals between visits are kept during the study. The number of treated is confirmed by counting at each visit and by cross-verification with the researcher. The staff member responsible for study supply handling is responsible for device accountability. Medical device accountability is recorded on a form not accessible to other staff members participating in the assessment of patients.

In addition to the routine monitoring procedures, a Good Clinical Practice (GCP) Quality Assurance audit is initiated and the purpose of audits is to evaluate compliance with the principles of GCP, international and local regulatory requirements, and the study protocol.

### Data collection and management

This study uses a newly created paper case report form (CRF) before the start of clinical trials according to the study protocol. The clinical research coordinator (CRC) of the clinical research center is responsible for CRF writing. After creating a CRF for all participants, data coding is performed.

Two independent entry staff enter into different databases, respectively. Check whether the entered data match using the verified SAS program (V.9.3 or later version), and if it does not match, check the data against the CRF to modify the data. Before entering into the database, set a minimum input rule and train the entry staff. Input rules can help improve the reliability of the input data by minimizing input errors that may occur when typing, and the entry staff is entered in line with the data entry standard operating procedures (SOP). If electronic data transmission is required, the DataBase Programmer (DBP) delivers the annotated CRF and table schema to the researcher.

For the protection of personal data and data security of the participants, physical security is maintained to prevent leakage of collected personal data. All participants’ paper CRFs and electronic documents are stored in a secure, access-controlled space or a locked file cabinet. Documents are stored and managed for 5 years after the completion of clinical trials.

### Randomization and blinding

This study is a multicenter, parallel-group, and single-blind trial. For this clinical trial, participants who meet all of the participants’ inclusion/exclusion criteria and agree to participate in this study are assigned to two groups, an experimental group and a control group, according to a randomization table. Randomization is performed by an independent statistician using a random number generator computerized by the block randomization method in SAS version 9.4 (SAS Institute Inc. Cary, NC, USA) or later. A separate randomization file is created for each research institute. Outcome evaluators were blinded for reducing the bias. In order to increase reliability by minimizing measurement error, the physical therapists with more than 5 years of experience conducted interventions and evaluations. At enrollment, we instructed patients not to reveal their allocation arm to the outcome evaluator. The blinding was achieved by allocating the tasks of study device handling and dispensation to an independent study team member who was unblinded and who was provided with the randomization schedule.

Randomization plans may be viewed in case of emergency such as a serious adverse event (SAE) when the blind should be removed for any participant. In this case, we will describe the reasons why randomization should be released, the procedure, the documentation required, the series of treatments, and the evaluation of the participants.

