## Method/design

### Study design

This study on the efficacy and safety of electromechanical-assisted gait trainer EXOWALK ® (HR-01) is a multicenter, randomized, superiority, and parallel-group study with a 1:1 allocation ratio. All enrolled participants are patients with stroke. Three clinical research centers in Korea participate in this trial: Dongguk University Ilsan Hospital, Chungnam National University Hospital, and Seoul National University Bundang Hospital. The 144 participants who met the inclusion criteria were assigned 72 each to the test and control groups. If the study protocol is changed, the changes and reasons are delivered by e-mail to the research participating organizations. The changed research protocol is submitted to the IRB for deliberation.

A strategy to achieve adequate participant registration is to promote the installation of posters and hand-outs in hospitals for patients and visitors to view. Each participant provides informed consent before enrollment. The research director explains the contents of the consent form to the patient for 30 min using terms that are easy for the general public to understand. We identify the schedule of the participants and schedule a visitable date to prevent participants from dropping out and complete the follow-up. Also, when the date of the visit approaches, we inform the participants in advance.

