### Sample size

The primary endpoint is the FAC difference before and after training. Data were available on this parameter from a previous trial (Hiroko Watanabe et al. 2014). Hiroko Watanabe et al. show a study on the improvement of stroke walking ability using the hybrid assisted limb (HAL), a representative device of the walking rehabilitation robot. According to the reference, the mean change in existing medical devices was 0.54 and 1 in the test group and HAL group. The newly developed medical device for use in this study was expected to produce about 25% better results in performance than in the HAL group, assuming a variation of 1.25. Therefore, it was assumed that the difference between the variation in the FAC of the test medical device and the comparator device was 0.71 and that the standard deviation was conservatively approached to assume the largest value of 1.4. Two-sided tests were used for sample size estimation. The number of participants per group to achieve overall power of 80% under the significant level of 0.05 is 65. To allow for a possible 10% dropout rate, 144 people were registered per group with 72 people.

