### Statistical analysis

Categorical variables such as gender, joint problem disorder, the cause of the disability, and paralysis side in demographic and clinical characteristic information will be presented as *n* (%). The pre-homogeneity will be analyzed by the chi-squared test or Fisher’s exact test. Continuous variables such as age, height, weight, the possibility of expression of intention, and the lower limb spasticity MAS score will be expressed as mean ± standard error (SE) and range. The pre-homogeneity will be analyzed using Student’s *t*-test or Wilcoxon’s rank sum test depending on whether the normality assumption is satisfied.

For all continuous variables of primary and secondary outcomes, the post-treatment measurement results will present the technological statistics, the observed number of patients, mean, SE, and range and compare the differences between groups using Student’s *t*-test or Wilcoxon rank sum test depending on the satisfaction of the normality assumption. The comparison analysis of differences before and after treatment in the group will be conducted using either the paired *t*-test or Wilcoxon’s signed tank test depending on the satisfaction of the normality assumption. In analyzing continuous variables, analysis of covariance (ANCOVA) will be performed after setting the variables as covariates when there are variables that seem to require control in the pre-homogeneity results for demographic and clinical characteristics.

Additional details regarding subgroup and adjusted analyses and definition of analysis populations are available in the clinicaltrials.gov (KCT0003411) in the study summary.

All data will be analyzed using SAS version 9.4 or later. All statistical tests will be two-sided, and the level of significance was set at 0.05.

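### Randomisation is blocked within centre, but the stated between-group tests ignore centre; if centres differ in FAC change, the tests are conservative and some precision is forgone

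*Protocol article*

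**What the plan says.** Under Randomization and blinding, the protocol article has an independent statistician prepare the allocation "using a random number generator computerized by the block randomization method in SAS version 9.4" or later, and adds: "A separate randomization file is created for each research institute". Study design names three hospitals and describes a "parallel-group study with a 1:1 allocation ratio".

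Under Statistical analysis, the continuous primary and secondary outcomes are compared between arms by Student's t-test or the Wilcoxon rank sum test, depending on normality. Covariates enter only by an ANCOVA that is run after "setting the variables as covariates when there are variables that seem to require control in the pre-homogeneity results" for demographic and clinical characteristics. The characteristics named there and under Outcome measurements do not include centre. The same section refers readers to the registry's study summary for further detail on adjusted analyses; that summary is not part of the document.

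**The concern.** Separate blocked lists force near-equal arm sizes within each hospital. Differences between hospitals in case mix, therapists or evaluators are thereby removed from the treatment contrast. A t-test or rank sum test that ignores centre still counts those differences as error. The reported standard error then overstates the true one, so p-values are too large and confidence intervals too wide for the design that was used.

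The adjustment rule does not repair this. It looks for baseline imbalance between arms, and within-centre blocking is there to prevent imbalance in centre. A prognostic stratification factor is thus the kind of variable that such a rule tends to miss.

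**Working it through.** **Inputs from the article (Sample size).** Difference in FAC change: "the difference between the variation in the FAC of the test medical device and the comparator device was 0.71". Standard deviation: "the standard deviation was conservatively approached to assume the largest value of 1.4". Sidedness: "Two-sided tests were used for sample size estimation". Result: "The number of participants per group to achieve overall power of 80% under the significant level of 0.05 is 65", raised to 72 per group (144 in total) for 10% dropout.

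**Reproducing the stated size.**
- Normal approximation: 2 × (1.4 × (1.960 + 0.842) / 0.71)² = 61.03, so 62 per group.
- Exact two-sample t-test: 62.01, so 63 per group.
- With the Wilcoxon efficiency of 3/π = 0.955: 62.01 / 0.955 = 64.9, so 65 per group.
- Dropout: 65 × 1.1 = 71.5, so 72 per group.

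The stated 65 is therefore reproduced. It is a plain two-group calculation on the total SD of 1.4 and takes no credit for stratification.

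**Assumed input.** r is the share of the variance in FAC change that lies between centres. The article gives no centre variance or intraclass correlation, so a range from 0 to 20% is used. The total SD is held at 1.4, and arms are taken as balanced within centre.

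**Formulas**, with n per group:
- SE reported by the unadjusted test: SE = 1.4 × sqrt(2/n), which is 0.2456 at n = 65 and 0.2333 at n = 72.
- True SE under within-centre balance: SE × sqrt(1 − r).
- Excess of reported over true SE: 1/sqrt(1 − r) − 1.
- True type I error of the unadjusted test: 2 × (1 − Φ(1.96/sqrt(1 − r))).
- Power ignoring centre: Φ((0.71/SE − 1.96)/sqrt(1 − r)).
- Power including centre: Φ(0.71/(SE × sqrt(1 − r)) − 1.96).

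**Example, r = 10%, n = 72.** 0.71/0.2333 = 3.043 and sqrt(0.9) = 0.949. Ignoring centre: (3.043 − 1.960)/0.949 = 1.14, power 87.3%. Including centre: 3.043/0.949 − 1.960 = 1.25, power 89.4%. Type I error: 1.960/0.949 = 2.07, giving 3.9%.

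| r (assumed) | SE too large by | True type I error | Power at 65 per group, ignoring / including centre | Power at 72 per group, ignoring / including centre |
|---|---|---|---|---|
| 0% | 0% | 5.0% | 82.4% / 82.4% | 86.1% / 86.1% |
| 5% | 2.6% | 4.4% | 83.0% / 84.3% | 86.7% / 87.7% |
| 10% | 5.4% | 3.9% | 83.7% / 86.2% | 87.3% / 89.4% |
| 20% | 11.8% | 2.8% | 85.1% / 89.8% | 88.7% / 92.5% |

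**Simulation check.** 20,000 trials per setting were run with three centres of 24 per arm, comparing a t-test with a linear model that includes centre. For r = 0, 5%, 10% and 20%, type I error of the t-test was 5.0%, 4.5%, 3.7% and 2.7%. Power ignoring / including centre was 85.7% / 85.7%, 86.2% / 87.3%, 87.1% / 89.1% and 88.2% / 92.2%. At r = 10% the mean unadjusted SE was 0.233, against an observed spread of the estimates of 0.221. This agrees with the formulas.

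**The case against.** The strongest objection is that the article refers further detail on adjusted analyses to a registry summary that is not shown, and that an article may leave model terms to a fuller plan. Centre may be handled there. This lowers confidence but does not remove the point: the article does not stay silent on the analysis. It names a test and a covariate rule, neither of which is likely to use centre, and nothing says that the registry text replaces them.

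Three stronger readings are tempting, and the document does not support them.
- A reader might infer that power built into the design is lost. It is not. The sample size uses the total SD, and unadjusted power stays at about 82% or more at 65 per group for every r considered. Only extra power is forgone.
- A reader might infer that the standard errors are certainly too large. That depends on centres differing in FAC change, for which the article gives no figure. Stable case-mix differences partly cancel in a change score, and the article asks for experienced therapists and evaluators at all sites. At r = 2% the difference at 72 per group is only 86.3% against 86.7% power.
- A reader might infer that the ANCOVA rule can never select centre. The trigger rests partly on judgement, and unfilled blocks or dropout can leave some imbalance. Unlikely is as far as the text goes.

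It also stands that the error is on the safe side: no bias and no excess of false positives.

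**Conclusion.** The point holds as a mismatch between design and analysis: allocation is stratified by centre, and the stated between-group tests ignore it. The size is modest and conditional. If centre explains 5% to 20% of the variance in FAC change, standard errors are 2.6% to 11.8% too large, and a nominal 5% test runs at about 4.4% to 2.8%. About 1 to 4 power points are forgone at 72 per group, or about 1 to 5 at 65. If centre explains nothing, nothing is forgone. The planned 80% power is intact throughout.

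These figures rest on the assumed range for r, on a total SD of 1.4 and on near-exact balance within centres. How the unseen registry summary treats centre remains open.

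**What to change.** State in the Statistical analysis section that the primary and secondary between-arm models include centre as a fixed effect with three levels, whatever the baseline homogeneity tests show. Where a rank test is used, make it a centre-stratified (van Elteren) test. Make this wording consistent with the registry's text on adjusted analyses, or, if centre is deliberately left out, say why.

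The cost is two degrees of freedom (140 instead of 142 residual degrees of freedom with 144 participants) and a sentence of analysis wording. No new data are needed and recruitment, which the article reports as complete, is unaffected. The change should be dated before outcomes are compared by arm. Whether to adjust for each outcome's baseline value as well is a separate question that the stratification argument does not settle.

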### Treatment and assessment

Treatment and assessment were done by different physiotherapists with 5 years or more of experience, to increase the reliability by minimizing the measurement error. The experimental group received electromechanically assisted gait training with EXOWALK and the control group received conventional gait training by therapists (Fig. 1). Conventional gait training consisted of physical therapist-assisted gait training by verbal command and physical contact. Patients in both groups were given 30 min of training per session, five times per week for 4 weeks (Fig. 1). Both groups continued to have other physical and occupational therapy.

**Fig. 1 Fig1:**
[figure not shown]
Flow chart for the protocol

The intervention presented in this study, electrochemical-assisted gait training, is a treatment that has already been verified and applied clinically and is currently applied to stroke patients in research institutes. There are no expected side effects from academic research to verify the effectiveness of electromechanical-assisted gait training from various angles. However, due to the nature of the robot, a large amount of treatment is performed compared to conventional training, which can lead to weak muscle spasms and fatigue. To prevent this, training is conducted with sufficient rest according to the instructions of a professional therapist.

#### Existing rehabilitation treatment

All patients in both groups undergo the existing rehabilitation treatment. The existing rehabilitation consists of neurodevelopmental treatment (NDT) and strength training. NDT is a rehabilitation treatment that induces the balance and control of sitting and standing postures by activating the reflex action of the paralyzed lower limb using the Bobath technique. Strength training is a mobility exercise to increase the range of motion of the paralyzed muscles and strength training to improve strength.

#### Electromechanical-assisted gait training

As a treatment performed in the experimental group, the patients perform the electromechanical-assisted gait training in addition to the existing rehabilitation treatment. The medical device is EXOWALK® (HR-01), a rehabilitation robot for the lower limbs under clinical trials.

#### Conventional gait training

As a treatment performed in the control group, the physiotherapist guides and walks the patient while assisting on the side or back of the participants.

### Outcome measurements

In this study, the demographic and clinical characteristics of the participants are measured and documented after screening. Demographic information record gender, date of birth, height, weight, and joint problems or not. And clinical characteristics record a total of five screening criteria. Screening criteria are the name of the diagnosis, cause of the disabilities (brain infarction, cerebral hemorrhage), the paralysis side (Rt., Lt., both, quadriplegia), the possibility of expression of intention (standard: MMSE 10 or higher), and the lower limb spasticity MAS score (standard: MAS grade 2 or lower).

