## Background

Gait training following a stroke has the potential benefits to increase walking speed as a result of training results in similar improvements in walking quality and economy [1]. For gait rehabilitation, highly repetitive practice restores gait function [2]. A number of rehabilitation robots consisting of treadmill and exoskeleton have been developed to assist people with brain lesions in walking training, mainly in Europe and the USA, and some have been commercialized. Automated electromechanical gait training devices were developed to reduce dependence on therapists [3].

Electromechanical-assisted gait training that requires repetitive tasks can improve the neuro-plasticity with motor learning focus on the reorganization of brain tissue, resulting in better balance and faster gait speed [4]. Seven papers concluded that the group that received the walking rehabilitation robot treatment in the 2017 Cochran review was more effective than the group that received the conventional gait rehabilitation treatment, and six papers did not [5]. Many of evidence suggests that high-intensity repetitive task-specific practice might be the most effective strategy to promote motor recovery after stroke, and therefore, electromechanical-assisted gait training represents one of the treatment options [6]. The previous study of this device revealed that electromechanically assisted gait training for 30 min each day for 5 days a week for a period of 4 weeks was as effective as gait training by a physical therapist [7]. A recent study reported the effectiveness on gait function of electromechanically assisted gait training with chronic stroke patients [8].

Conventional gait training conducted by a physical therapist was a standard method of gait training for stroke patients. After the introduction of robot rehabilitation, many studies investigated the effectiveness of electromechanically assisted gait training by comparing it with that of conventional gait training [5]. However, many studies still have difficulty to clarify the difference between conventional gait training and electromechanically assisted gait training and besides presented one of the reasons for the limitation of insufficient participants [9–11]. Now we need to conduct a large-scale randomized design to determine the effectiveness of electromechanical-assisted gait training by comparing it with physical therapist-assisted conventional gait training.

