### Inclusion/exclusion

The patients are screened for a stroke, 10 or more Mini-Mental State Examination (MMSE), Modified Ashworth Scale (MAS) grade 2 or lower, and standing with an assist. The following patients are excluded: (1) patients with poor cognition that are difficult to carry out instructions; (2) ataxia; (3) patients with MAS grade 3 or above; (4) patients with severe leg arthritis; (5) difficulty walking due to joint swelling of the lower leg; and (6) situations where other walking training cannot be performed.

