## Discussion

Automated electromechanical gait training devices have been developed and their effectiveness has been proven [12, 13]. However, other reports documented similar or superior effects of robot-assisted therapy in combination with conventional physiotherapy versus conventional therapy alone on gait recovery, especially in patients with sub-acute stroke [14, 15]. This clinical study aims to certify a recently developed medical device and demonstrates the safety and efficacy of EXOWALK, an electromechanical-assisted gait trainer, in stroke patients.

There are still sufficient papers on the effectiveness of electromechanical-assisted gait training for domestic patients and large-scale research is lacking. Thus, the research described here is a large-scale study of domestic patients that can supplement the limitations mentioned in other previous studies. In addition, the clinical studies described here include physical epidemiological analysis parameters that can determine walking ability. Therefore, it can prove that robotic therapy is effective for walking. The clinical is a multicenter study for domestic patients conducted by all three institutions in a thorough random sampling system, so it will be possible to prove its generalizable effectiveness and safety.

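### Time since stroke is neither limited at entry nor listed among the recorded characteristics, so under the stated rule it cannot be a covariate or show to which stroke phase the result applies

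*Protocol article*

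**What the plan says.** **Eligibility.** The Study design section describes the population only by diagnosis: "All enrolled participants are patients with stroke". The Inclusion/exclusion section adds cognition, spasticity and standing ability: "The patients are screened for a stroke, 10 or more Mini-Mental State Examination (MMSE), Modified Ashworth Scale (MAS) grade 2 or lower, and standing with" assistance. None of the six exclusions concerns time since the stroke.

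**Baseline record.** Outcome measurements gives two lists. The demographic one reads: "Demographic information record gender, date of birth, height, weight, and joint problems or not". The clinical one is counted: "And clinical characteristics record a total of five screening criteria". Its items are diagnosis, cause (infarction or haemorrhage), side of paralysis, the MMSE criterion and the MAS score. Neither list has a stroke date. The only onset mentioned in the article, under Safety assessment, belongs to clinical alterations seen during the trial.

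**Randomisation.** Blocks within centre: "A separate randomization file is created for each research institute". No other stratification factor is named.

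**Analysis.** Groups are compared by t-test or Wilcoxon rank sum test. ANCOVA is used only when the baseline comparison of demographic and clinical characteristics points to a variable needing control. For subgroup and adjusted analyses the article refers to the registry summary.

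**Phase in the article's own argument.** The Background cites a study of "electromechanically assisted gait training with chronic stroke patients". The Discussion cites reports on robotic plus conventional therapy whose effects were seen "especially in patients with sub-acute stroke".

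**The concern.** Entry is open to patients at any interval after stroke. If spontaneous recovery of walking differs by phase, part of the spread in FAC change over the four weeks of training and the four weeks of follow-up comes from phase and not from treatment. A trial that records the onset date can remove that part by adjustment, show whether the arms were alike, and tell readers what mix of patients was studied. A trial that does not record it can do none of these.

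The last loss needs no numerical assumption. The Discussion aims at generalisable effectiveness, and the article sets its rationale against separate sub-acute and chronic evidence. Without time since onset, the result cannot be placed against either body of evidence.

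**Working it through.** **1. The plan's own figure.** Inputs from Sample size: difference 0.71, SD 1.4, two-sided alpha 0.05, power 80%.

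- Normal approximation: n = 2 × [1.4 × (1.960 + 0.842) / 0.71]² = 61.03, so 62 per group.
- Two-sample t-test: 62.01, so 63.
- t-test figure divided by the Wilcoxon relative efficiency of 0.955: 64.9, so 65, the stated number.
- Dropout: 65 × 1.10 = 71.5, so 72 per group and 144 in total, as stated (65 / 0.90 would give 73).

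The stated size is adequate on its own inputs, and nothing here disputes it. Power at 65 per group is Φ(0.71 / [1.4 × √(2/65)] − 1.96) = Φ(0.93) = 82%.

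**2. Variance explained by phase.** The documents give neither the share of sub-acute patients (p) nor the gap in mean FAC change between phases (d). Both are assumed: p from 0.3 to 0.5, d from 0.5 to 1.0 FAC level. The planned SD of 1.4 is taken as the total SD in the mixed population, so its variance is 1.96. The share is R² = p(1 − p)d² / 1.96. Adjusted power uses SD = 1.4 × √(1 − R²) at 65 per group.

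| p | d | R² | Power after adjustment |
|---|---|---|---|
| 0.3 | 0.5 | 0.21 × 0.25 / 1.96 = 2.7% | 83% |
| 0.3 | 1.0 | 0.21 × 1.00 / 1.96 = 10.7% | 86% |
| 0.5 | 0.5 | 0.25 × 0.25 / 1.96 = 3.2% | 84% |
| 0.5 | 1.0 | 0.25 × 1.00 / 1.96 = 12.8% | 87% |

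The gain is for phase alone. If baseline FAC already carries part of the phase information, the gain beyond an analysis adjusted for baseline FAC would be smaller.

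**3. Chance imbalance.** With 72 per arm and p = 0.5, ignoring blocking by centre, the SD of the difference in sub-acute share is √(2 × 0.25 / 72) = 0.083. An imbalance of 10 percentage points or more, in either direction, has probability 2 × [1 − Φ(0.10 / 0.083)], about 23%. At d = 1.0, a 10-point imbalance moves the arm difference by 0.10 × 1.0 = 0.10 FAC level, which is 0.10 / 0.71 = 14% of the planned effect.

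That shift should be read against the standard error of the difference, 1.4 × √(2/72) = 0.233. It is 0.10 / 0.233 = 0.43 of one standard error, and chance shifts of this kind are already part of that standard error.

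**4. Can the stated rule reach the variable?** The trigger for ANCOVA is a baseline comparison of demographic and clinical characteristics. Time since onset is on neither list in Outcome measurements, so it cannot be compared at baseline and cannot trigger or enter the adjustment.

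**The case against.** **The list may not be closed.** The count of five refers to screening criteria, and the list does not cover even all entry conditions: standing ability and ataxia are missing from it. The Statistical analysis section introduces its baseline variables as examples. The paper case report form is not shown, and the article refers subgroup and adjusted analyses to the registry. All of this stands: an onset date may exist in a document not at hand, so the finding is limited to the plan as written. The article does, however, state a total and name the items, which is more than ordinary condensation.

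**The effect is small and assumed.** This stands too. The documents support the relevance of phase only qualitatively, and a 1.0-level gap exceeds the whole planned treatment effect of 0.71. Power is about 82% without adjustment, and the SD was set at the largest value considered.

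**Broad entry is a choice.** That is fair. Mixing phases is consistent with the aim of generalisable results and is not an error in itself.

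**Stronger readings.** A reader might infer that the comparison is biased, or that phase can be neither balanced, adjusted for nor examined. The documents do not support either inference. Randomisation within centre balances phase in expectation, and type I error is unaffected; only stratification by phase is absent. Stroke dates can probably still be obtained from hospital records, since the Screening section says that screening draws on hospital data. If so, adjustment and examination remain possible once the item is added.

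**Conclusion.** The point holds as a cheap improvement to precision and interpretability, not as a threat to validity. As written, entry has no time-since-stroke limit, the counted clinical list omits onset, and the covariate rule cannot reach it.

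Under the assumed gaps of 0.5 to 1.0 FAC level and a sub-acute share of 30 to 50%, phase would account for about 3 to 13% of the planned variance. At an even mix, adjustment would take power at 65 per group from about 82% to 84–87%. These figures depend on assumptions that the documents neither confirm nor exclude. The inability to say which stroke phase the result describes depends on none of them, only on the onset date not being held elsewhere.

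**What to change.** 1. State whether the case report form holds the date of stroke onset. If it does not, abstract it from the hospital record for all 144 patients, without reference to allocation and before unblinding.
2. Report time since onset by arm with the other baseline characteristics.
3. Amend the Statistical analysis section. It has no primary ANCOVA at present, so adding a covariate is not enough: replace the imbalance-triggered ANCOVA with a pre-specified ANCOVA of FAC that includes baseline FAC, centre and log time since onset.
4. Tabulate the treatment effect by stroke phase, labelled as exploratory, with the phase cut-point fixed in advance.

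The cost is one abstracted item per patient and an amendment to the analysis text, including the change of primary model. The sample size does not change. Eligibility and stratification also stay as they are, because Trial status reports that recruitment is complete. If outcomes by arm have already been seen, the adjusted result can still be given but should be labelled post hoc.
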